### Quality control methods

The principal investigator or study coordinator will review all CRFs and data within the study database for completeness and accuracy on an annual basis. Recruitment will also be monitored on an annual basis.

### Assessment of results

The primary outcomes will be the feasibility and safety of partial heart transplantation. The feasibility will be determined by the ability to perform the new operation in at least one patient per year for three years after enrollment opens. The safety of the procedure will be indicated by survival and re-interventions that are the same or are better than those reported in the literature for patients of similar age undergoing conventional valve replacement. Safety will primarily be defined as patient survival or re-operation or transcatheter reintervention on the transplanted valve at six-month intervals, starting six months after the first subject undergoes a valve transplant, and continuing until one year after all five subjects have been enrolled. Safety will also be assessed by tracking rates of immunosuppression side effects, including development of insulin-dependent diabetes, chronic renal insufficiency, and significant infections.

The secondary outcomes will be valve annulus growth over time, stenosis and regurgitation. The valve annulus diameter will be measured using echocardiography in two planes at baseline and every six months following the operation. The valve annulus Z-score should remain relatively unchanged over time, indicating an increase in valve annulus growth corresponding with an increase in body surface area. This change should correspond to the growth of conventional heart transplants and Ross pulmonary autografts [18–20]. Valve stenosis and regurgitation will be assessed via transthoracic echocardiogram with pulse Doppler and with color Doppler, respectively, every six months following the operation.

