## Materials and methods

### Study design

A prospective nonrandomized, single-center, single arm pilot trial will be performed in infants and young children who require semilunar heart valve replacement. The study received approval from the Medical University of South Carolina (MUSC) Institutional Review Board Protocol Record 00114653 and the protocol was registered and approved on the ClinicalTrials.gov platform, trial number NCT05372757. The schedule of enrolment, interventions and assessments is shown in Fig 1.

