### Study population

Five patients in need of a heart valve replacement will be included in the study. A study investigator who normally participates in our biweekly pediatric heart center case conference meeting and has access to patient records and surgical referrals for valve replacement will identify potential candidates for the trial. Study investigators will obtain permission from the primary cardiologist or cardiac surgeon prior to approaching parents or legal guardians to discuss participation in the trial. Telemedicine may be utilized to initially discuss the risks and benefits associated with the study with parents or legal guardians of potential subjects who are outpatients, but an in-person meeting will be required for a formal consent discussion. Expectant mothers who are carrying fetuses that are expected to require heart surgery requiring a valve replacement within the first two years of life may be approached for enrollment in the study as well.

The interventional portion of the study will take place in the cardiac operating rooms and in the Pediatric Cardiac Intensive Care Unit at Shawn Jenkins Children’s Hospital at MUSC. Additional observational data will be collected pre- and intraoperatively, and postoperatively on the Cardiac Stepdown Unit and in the outpatient cardiology clinics at MUSC’s Summey Medical Pavilion.

To be eligible to participate in this study, the patients can be either male or female and must meet the following inclusion and exclusion criteria:

Inclusion Criteria

Children less than 2 years of age who are referred for a cardiac operation that involves a primary semilunar valve replacement, or children less than 2 years of age who are referred for a cardiac operation involves an initial replacement of a previously placed prior homograft, bioprosthetic, or mechanical valve in the aortic or pulmonary positionDeemed acceptable for partial heart transplantation based on the standard evaluation process used for conventional orthotopic heart transplantation at our center (see S1 Appendix)Have insurance approvalProvide written informed consent of both parents or legal guardians; if there is only one parent or legal guardian, consent from that individual will be adequate.

Exclusion Criteria

Absolute contraindications for conventional orthotopic heart transplantation:

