### Data analysis

Data will be exported from the study database for statistical analysis. Given the goal sample size of five participants and lack of control group, simple descriptive statistics will be used.

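### The same-or-better safety criterion asks five uncontrolled patients for a comparison with the literature that they cannot support

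*Protocol article*

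**What the plan says.** The protocol article makes feasibility and safety the primary outcomes (Assessment of results). Survival and re-interventions are to indicate safety if they prove "the same or are better than those reported in the literature for patients of similar age undergoing conventional valve replacement". The next sentence gives the measure: "Safety will primarily be defined as patient survival or re-operation or transcatheter reintervention on the transplanted valve at six-month intervals". The readings begin half a year after the first transplant, "continuing until one year after all five subjects have been enrolled". Immunosuppression side effects are tracked as a further part of safety.

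The size is set in Study population: "Five patients in need of a heart valve replacement will be included in the study". Study design describes a nonrandomized, single-centre, single-arm pilot. Data analysis reads: "Given the goal sample size of five participants and lack of control group, simple descriptive statistics will be used".

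The article names no published rate, no margin and no number of events that would count against the operation.

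**The concern.** A comparative criterion is attached to a primary outcome, but neither the sample nor the analysis can carry a comparison. With no tolerance stated, the only comparison the text supports is the observed proportion in five patients against a published proportion. The observed proportion can only be 0, 20, 40, 60, 80 or 100%.

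This is a new operation with immunosuppression in children under two. A result of 0 of 5 could be reported as meeting the stated safety criterion while a high true risk is not excluded. A result of 1 of 5 could be reported as missing it when the operation is no worse than conventional replacement. The Introduction adds to the risk, because it says the trial will test a central hypothesis of superior outcomes over available implants.

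The outcome sentence has a separate fault. It links patient survival, re-operation and transcatheter reintervention with the word or. Taken literally, a patient who survives untouched and a patient whose valve is re-operated both meet it.

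**Working it through.** There is no stated power, margin or benchmark, so there is no figure of the plan's own to reproduce.

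**Inputs**
- n = 5, single arm (Study population, Study design).
- Criterion: same as or better than the literature, with no margin (Assessment of results).
- Benchmark event rate p0: not given. Assumed values from 5% to 40% over the follow-up window.
- Outcome for the main calculation: one composite of death, re-operation or transcatheter reintervention.

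**Step 1. What five patients can show.** Exact (Clopper-Pearson) 95% intervals:
- 0/5: upper limit 1 − 0.025^(1/5) = 0.522, so 0% to 52%.
- 1/5: 0.5% to 72%.
- 2/5: 5% to 85%.

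Even the best possible result, 0/5, leaves every benchmark below 52% inside the interval.

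**Step 2. The criterion as a raw comparison.** Pass if events/5 ≤ p0, so the number of events allowed is c = floor(5 × p0). With X ~ Bin(5, p):
- chance that an equally safe operation fails = 1 − P(X ≤ c | p = p0);
- chance that one with twice the risk passes = P(X ≤ c | p = 2p0).

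Worked at p0 = 10%: c = 0. Fail if equal = 1 − 0.9^5 = 1 − 0.590 = 41.0%. Pass if doubled = 0.8^5 = 32.8%.

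Worked at p0 = 20%: c = 1. Fail if equal = 1 − (0.8^5 + 5 × 0.2 × 0.8^4) = 1 − 0.737 = 26.3%. Pass if doubled = 0.6^5 + 5 × 0.4 × 0.6^4 = 33.7%.

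| Assumed p0 | Events allowed | Equally safe, fails | Twice the risk, passes |
|---|---|---|---|
| 5% | 0 | 22.6% | 59.0% |
| 10% | 0 | 41.0% | 32.8% |
| 15% | 0 | 55.6% | 16.8% |
| 20% | 1 | 26.3% | 33.7% |
| 25% | 1 | 36.7% | 18.8% |
| 30% | 1 | 47.2% | 8.7% |
| 40% | 2 | 31.7% | 5.8% |

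The figures jump where one more event becomes allowed. For any benchmark below 20% a single event fails the criterion, because 1/5 = 20%. Just below that step, at 19%, the two chances are 65.1% and 9.2%, so the tabulated 23% to 56% is not an upper bound for every value in between.

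**Step 3. Two outcomes instead of one.** If death and re-intervention must each pass, and are taken as independent:
- Benchmarks 5% and 20%: equally safe fails 1 − 0.774 × 0.737 = 43.0%; both doubled passes 0.590 × 0.337 = 19.9%.
- Benchmarks 10% and 20%: equally safe fails 56.5%; both doubled passes 11.0%.

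Over the seven benchmark pairs run, an equally safe operation failed 43% to 77% of the time, and one with both risks doubled passed about 2% to 20% of the time.

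**The case against.** The best defence is that the article already treats itself as a pilot. Data analysis restricts itself to description and gives the reason, and the Discussion defers extensive analysis to a larger sample. Continuation and suspension rest with the DSMB, the IRB and the investigators' risk/benefit reviews, not with this criterion. Immunosuppression side effects also count toward safety. The pass/fail rule computed above, including its benchmarks, is a reading of the text and is not printed in it. Exact intervals and a named benchmark could sit in an analysis plan that is not shown.

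Much of this stands as a limit on the point. Four stronger readings are tempting, and the document does not support them:
- *That the trial will formally declare the operation safe.* The verb used is that safety is indicated, and no trial decision is tied to it.
- *That the criterion often passes an operation with twice the risk, whatever the benchmark.* The chance is substantial only for some assumed benchmarks up to about 20%. It is already 17% at 15%, and it is under 10% at 30% or more.
- *That the outcome cannot be counted.* It is mis-worded, but the preceding sentence makes its components and their favourable direction clear, and each can be counted.
- *That five patients is itself the error.* A five-patient pilot is a legitimate design. The fault is the comparison attached to it.

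What the defence does not do is withdraw the criterion. Neither the pilot label nor the restriction to description nor the Discussion changes the sentence that makes same-or-better results the indicator of a primary outcome. An analysis plan that named a benchmark would not rescue the comparison at n = 5.

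**Conclusion.** The point holds. As written, the criterion can yield a comparative statement about safety that five uncontrolled patients cannot support. The intervals in Step 1 need only n = 5 and are firm. The misclassification figures rest on three assumptions: a raw comparison, a single composite, and benchmarks that the document does not supply. Within those, the failure of an equally safe operation is large at every benchmark tabulated. The passing of a doubled risk depends strongly on the benchmark and should be quoted only with its range. Requiring both outcomes to pass lowers the second error but raises the first. The outcome wording is a smaller fault that the same edit can correct.

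**What to change.** In Assessment of results:
1. Define the primary safety outcome as death, re-operation or transcatheter reintervention on the transplanted valve. Show death and reintervention separately as well.
2. Report counts with exact 95% intervals at 6 and 12 months after transplant.
3. Run the primary safety window to 12 months after the last transplant. The present window closes one year after the last enrolment. Because subjects may wait on the list after enrolling (Preoperative procedures), a late transplant may not reach 12 months inside it. The follow-up in Late postoperative procedures, twice a year until one year after the transplanted valve is replaced, already covers the longer window.
4. Show any published rate as context only.
5. Replace the same-or-better criterion with a statement that the trial estimates these rates and will not conclude equal or better safety.

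The tracking of immunosuppression side effects stays as it is. The change needs no extra patients, tests or procedures, only revised wording and an exact-interval calculation. The price is a weaker stated safety claim and, if the last transplant comes well after enrolment, a later close of the primary safety window.

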#### Preoperative procedures

Written informed consent for partial heart transplantation will be obtained from the parents or legal guardians of each subject. Potential subjects and their parents or legal guardians will undergo a full evaluation for candidacy for partial heart transplant using well-established criteria and workflows for infants and young children who are being assessed for conventional heart transplantation. These patients will be listed for partial heart transplant using pre-established mechanisms similar to conventional heart transplantation via the regional South Carolina organ procurement network, We Are Sharing Hope.

For a subject to be enrolled in the trial, a time window will be established by an attending pediatric cardiologist as to how long the subject can be listed for partial heart transplantation before a conventional valve replacement option is scheduled. This time window will be determined based on the subject’s clinical status and severity of valve dysfunction and may be revised over time based on evolving clinical status.

As is the case for patients undergoing conventional heart transplantation, donor hearts will be selected based on the recipient’s ABO blood group, PRA, weight, CMV status, and EBV status. Parents or legal guardians of enrolled subjects will be required to carry a transplant pager, consistent with established practice for patients who are listed for conventional heart transplantation.

When a donor heart becomes available, a focused echocardiogram will be performed on the donor heart to specifically assess the semilunar valve annulus size and function before the heart is accepted. The donor heart will be procured and transported to MUSC by our cardiac surgeons using practices consistent with those utilized for conventional heart transplantation. The donor semilunar valve will be excised from the donor heart by a pediatric cardiac surgeon. The heart valve will be accepted after it is visually inspected by the procurement team at the donor hospital.

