#### Operative procedures

Subjects will be scheduled for an emergent operation using established mechanisms. The recipient operation will not start until the donor valve is visually inspected and accepted by the MUSC procurement team. When the donor heart valve arrives in the MUSC operating room, the usual procedure for organ check-in will be followed (S1 Appendix).

The donor valve will be implanted into the recipient using techniques identical to those used for homograft semilunar valve replacement [16]. If for any reason the donor heart valve is unsuitable, a cryopreserved homograft valve will be implanted. Consistent with standard practice, a transesophageal or epicardial echocardiogram will be obtained in the operating room to assess valve and myocardial function before the sternotomy incision is closed.

Immunosuppression will be administered intraoperatively consistent with practices utilized for conventional heart transplantation, which typically includes administration of a calcineurin inhibitor such as tacrolimus, mycophenolate mofetil (MMF), and steroids [17].

Research data will be collected from the medical record, including the operative note (surgeon, surgical procedure, cardiopulmonary bypass time, cross-clamp time, ischemic time), and intraoperative echocardiogram (size and function of both the excised and newly implanted donor valve).

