### Data management methods

Data will be collected at intervals as described above. Descriptions of confidentiality provisions and data safety monitoring boards (DSMB) are provided in a later section. In order to preserve the confidentiality of the participants, the following interventions will be undertaken:

A. Case report forms (CRFs) will be developed prior to the onset of the trial and completed by a study investigator for each patient.
a. An enrollment form will be completed once written informed consent is provided by the parents or legal guardians.b. Adverse event forms will be completed as needed throughout the operative hospitalization.B. A dedicated Excel database will be developed for the trial.
a. All data from the CRFs will be entered into a dedicated Excel database by a study team member.C. In the case of a subject withdrawing from the trial, the data will be potentially included in the final analysis depending on the time enrolled in the trial.

Missing data will be addressed by omission or analysis as appropriate. Sensitivity analysis will be planned to avoid misleading inference when complete-case analysis is performed.

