### Possible risks to participants

This study involves greater than minimal risk with the potential for direct benefit. In conventional heart transplantation, the most serious risks are graft failure, cardiac allograft vasculopathy, infection and acute rejection, which altogether account for the majority of deaths after conventional heart transplantation. The relative importance of these causes of death vary over time post-transplant. Risks of partial heart transplantation are expected to be similar to the risks of standard valve replacement but less than the risks of conventional heart transplant. A complete list of risks is provided in S2 Appendix.

The most serious risks are scheduling issues related to donor heart availability and rejection of the transplanted valve. The risk of rejection is theoretically lower compared to a full heart transplant. The risk of death during and after the operation is similar to the risks for standard valve replacement with a homograft. There is no risk of disease developing in the blood vessels that supply the heart (i.e., coronary arteries) and no risk of heart muscle dysfunction given that these tissues are not being transplanted.The surgery will result in a permanent scar in the middle of the chest. This is the same scar that would result from a standard valve replacement or full heart transplant. This scar may require medical follow-up after surgery and may temporarily restrict the subject from exercise and/or sports participation in the future.Open heart surgery involves the risk of death, brain damage, or other organ damage such as kidney injury.The need for blood transfusion during surgery poses a risk of infection from the blood or a reaction to the blood. The risk of infection from transfused blood is extremely low given current screening processes.Patients receiving a partial heart transplant may also become sensitized to the transplanted valve tissue. This will decrease the donor pool if the patient ever requires a heart transplant.There is a risk of loss of confidentiality.There may also be additional risks that are currently unknown.

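### The primary safety window closes one year after the fifth enrolment, but the outcome it serves depends on transplant, and enrolled subjects may be transplanted late or never

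*Protocol article*

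**What the plan says.** **The count.** Study population: "Five patients in need of a heart valve replacement will be included in the study". Data analysis: "Given the goal sample size of five participants and lack of control group, simple descriptive statistics will be used". Neither place says whether the five are enrolments or transplants.

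**The window.** Under Assessment of results, "Safety will primarily be defined as patient survival or re-operation or transcatheter reintervention on the transplanted valve". It is read at six-month intervals, beginning six months after the first subject's transplant and "continuing until one year after all five subjects have been enrolled". The caption of Fig 1 gives the same stop rule. Survival and reintervention are to be judged against published results in children of similar age who had conventional valve replacement.

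**When enrolment happens.** Data management methods: "An enrollment form will be completed once written informed consent is provided by the parents or legal guardians". Study population also allows expectant mothers to be approached for enrolment when the fetus is likely to need a valve within two years of birth.

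**Routes to another valve.** Preoperative procedures has a cardiologist set "how long the subject can be listed for partial heart transplantation before a conventional valve replacement option is scheduled". Operative procedures adds: "If for any reason the donor heart valve is unsuitable, a cryopreserved homograft valve will be implanted".

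**Waiting as a risk.** Possible risks to participants: "The most serious risks are scheduling issues related to donor heart availability and rejection of the transplanted valve". Adverse event forms, under Data management methods, cover the operative hospital stay.

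**The concern.** The window's end is tied to one event and its content to another. A wait of unstated length lies between consent and transplant, and two written routes lead away from transplant altogether. Followed literally, the stop rule can close the primary safety window while a subject is still listed, or soon after that subject's operation. A subject who received another valve has no transplanted valve on which reintervention could be counted.

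Three things are at stake. The number of transplants behind the safety result may be below five without the article saying how that is to be shown. The post-transplant time behind the result may be short for exactly the subjects who waited longest. And with five subjects, whether one waiting death enters the survival figure could settle the comparison with the literature, yet the text does not say whether it does.

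**Working it through.** **1. The plan's own figure.** The article gives no alpha, power, effect or margin, so n = 5 cannot be reproduced by a sample-size formula. It is a goal for a descriptive pilot, and no stated number is wrong.

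**2. The elements of the safety outcome side by side.**

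| Element | Tied to |
|---|---|
| End of the window | fifth enrolment |
| Start of the window | first transplant |
| Reintervention | the transplanted valve |
| Comparator | children who had an operation |
| Adverse event form | operative hospital stay |
| Patient survival | not stated |

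**3. Post-transplant time inside the window.** Let E be the date of the fifth enrolment and T a subject's transplant date, in months. Time in the window after transplant is E + 12 − T. A full year needs T no later than E. For the fifth subject, with a wait of w months after consent, the time is 12 − w. The article gives no waiting times, so w is assumed:

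- w = 3: 9 months
- w = 6: 6 months
- w = 9: 3 months
- w = 12 or more: none

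The fifth subject thus loses the whole of its own wait from the year. So does any earlier subject still listed at E, for the part of the wait that runs past E.

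**4. Number transplanted.** Let p be the probability that an enrolled subject receives a partial heart transplant. It is not given; assume it equal and independent across subjects. Expected transplants = 5p, and the chance of all five = p^5. The feasibility criterion, one operation a year for three years, needs at least three; the last column gives that binomial chance and ignores the yearly timing.

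| p (assumed) | Expected | All five | At least three |
|---|---|---|---|
| 0.95 | 4.75 | 77% | 99.9% |
| 0.8 | 4.0 | 33% | 94% |
| 0.6 | 3.0 | 8% | 68% |
| 0.5 | 2.5 | 3% | 50% |

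**5. Precision with no events.** The upper end of the two-sided exact 95% interval is 1 − 0.025^(1/n): 52% for n = 5, 60% for n = 4 and 71% for n = 3. No planned decision uses these limits; they only show how little is left when transplants are lost.

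**6. A waiting death.** Suppose one of five dies while listed and four are transplanted and survive. Survival is 4/4 = 100% from transplant and 4/5 = 80% from enrolment. The safety definition fits either reading. If the death came before the first transplant, it also precedes every assessment point.

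**The case against.** A reader might infer that harm while waiting is shut out of the safety assessment. The article does not support that. Patient survival is not limited in words to transplanted subjects; the phrase about the transplanted valve most naturally qualifies the reinterventions. The calendar start means that a later subject's waiting death can fall inside the window. Under Confidentiality provisions, investigators monitor every study patient for adverse events, and the data safety monitoring board meets one month after each of the first three enrolments. A waiting death is therefore undefined, not excluded.

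A reader might also infer that the transplanted children are selected for being stable enough to wait, so that the literature comparison flatters the new operation. That is conjecture. The listing window follows clinical status and may be revised, and waiting could equally leave children sicker at operation.

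A shortfall in transplants would not be hidden either: feasibility is counted in operations performed, and nothing in the article plans to report fewer transplants as five. The value of p is assumed throughout, and the donor valve is inspected before the recipient's operation begins, which limits the in-theatre fallback. Late postoperative procedures also provides follow-up well beyond the window for transplanted subjects, so the loss is from the stated primary outcome and not necessarily from the records.

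Finally, analysis populations and replacement rules may stand in the full protocol or analysis plan, which is not shown, and their absence from an article is no fault. All of this stands. What it does not answer is the stop date, which the article itself fixes at the fifth enrolment.

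**Conclusion.** The concern holds as a mismatch within the stated primary safety outcome: an enrolment-based end date against a transplant-based start, reintervention measure and comparator. Within that window the fifth subject has a year after transplant less its own wait, and a subject who received another valve has no post-transplant time. Fewer than five transplants may be studied; the chance of this is 23% at p = 0.95 and 67% at p = 0.8, both values of p being assumptions. A death while waiting is undefined in the primary outcome. Deterioration or conversion while waiting has no place in it or on the adverse event form, although donor availability is listed among the most serious risks.

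The documents do not show that waiting harm is excluded, that the comparison is biased in a known direction, or that enrolment must continue until five are transplanted. At p = 0.5, five expected transplants would take 5/0.5 = 10 enrolments, twice the goal. Nor would the few subjects who convert to another valve make a usable concurrent reference group.

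**What to change.** In Assessment of results and the caption of Fig 1:

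- End the safety window one year after the last enrolled subject's transplant, or after final disposition if that subject is not transplanted.
- State the number transplanted beside the number enrolled wherever safety is reported.
- Follow every listed subject from listing, whatever valve is received, through the same medical record review.
- Report survival from listing for all listed subjects, with waiting deaths and conversions shown, beside survival from transplant.

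The enrolment goal can stay at five. The changes need wording, a somewhat longer window and a little more record review for the few subjects not transplanted. No study procedure is added, since the Treatment section already draws the research data from the medical record.
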